# Development and Management of Networks of Care at the End of Life (the REDCUIDA Intervention): Protocol for a Nonrandomized Controlled Trial

**DOI:** 10.2196/10515

**Published:** 2018-10-12

**Keywords:** palliative care, public health, delivery of health care, community networks

## Abstract

**Background:**

End-of-life needs can be only partly met by formalized health and palliative care resources. This creates the opportunity for the social support network of family and community to play a crucial role in this stage of life. Compassionate communities can be the missing piece to a complete care model at the end of life.

**Objective:**

The main objective of this study is to evaluate the REDCUIDA (*Redes de Cuidados* or Network of Care) intervention for the development and management of networks of care around people with advanced disease or at the end of life.

**Methods:**

The study is a 2-year nonrandomized controlled trial using 2 parallel groups. For the intervention group, we will combine palliative care treatment with a community promoter intervention, compared with a control group without intervention. Participants will be patients under a community palliative care team’s supervision with and without intervention. The community promotor will deliver the intervention in 7 sessions at 2 levels: the patient and family level will identify unmet needs, and the community level will activate resources to develop social networks to satisfy patient and family needs. A sample size of 320 patients per group per 100,000 inhabitants will offer adequate information and will give the study 80% power to detect a 20% increase in unmet needs, decrease families’ burden, improve families’ satisfaction, and decrease the use of health system resources, the primary end point. Results will be based on patients’ baseline and final analysis (after 7 weeks of the intervention). We will carry out descriptive analyses of variables related to patients’ needs and of people involved in the social network. We will analyze pre- and postintervention data for each group, including measures of central tendency, confidence intervals for the 95% average, contingency tables, and a linear regression. For continuous variables, we will use Student *t* test to compare independent samples with normal distribution and Mann-Whitney *U* test for nonnormal distributions. For discrete variables, we will use Mann-Whitney *U* test. For dichotomous variables we will use Pearson chi-square test. All tests will be carried out with a significance level alpha=.05.

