### Recruitment Procedure

Potential participants will receive information from palliative care team members. Reasons for declining to participate will be recorded as not interested, too busy, don’t believe in it, and other.

Palliative care teams will arrange an appointment with the patient for the baseline assessment. This first appointment will take place in the patient’s home. At this appointment, written informed consent for participation in the study will be obtained from participants.

Patients assigned to the intervention group will be those living in the San Pablo-Santa Justa area, Seville (60,000 inhabitants), who accepted the community promoter intervention. Patients assigned to the control group will be those living in an area with no community promoter available.

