### Sample Size Calculation

We have calculated a sample size of 320 patients per group for a population of 100,000 inhabitants based on the number of people dying of cancer each year (7000 people per million inhabitants) and the number of people in the final stage of nononcologic illnesses (approximately 4500 cases per million inhabitant). In a population of about 700 people, per year, 65% will require specialized palliative care (455 patients eligible for the study [41]).

We have considered that 30% of patients will not sign the informed consent forms or will not meet all the inclusion and exclusion criteria.

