## Discussion

### Beneficiary Population

Results from this study would be applicable among a vast population, including palliative care patients in developing countries. It is known that 7000 people per million population globally die each year, 2500 per million die of cancer, and approximately 4500 per million die in the final stage of any nononcologic illnesses [41]. It is estimated that 65% of this population will need specialized palliative care.

If our results confirm that community social networks improve patients’ and families’ satisfaction at the end of life and correlates with the best use of health system resources, new palliative care systems may be developed.

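### The 320 per group is a one-year count of available patients per 100,000 inhabitants, not a power calculation, so the abstract's 80% power is unsupported

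*Protocol article*

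**What the plan says.** The protocol article makes two statements about the group size.

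- Abstract, Methods: "A sample size of 320 patients per group per 100,000 inhabitants will offer adequate information and will give the study 80% power". The effect named is "to detect a 20% increase in unmet needs". The same sentence extends the 80% to family burden, family satisfaction and health-system use, with no effect size for any of them.
- Sample Size Calculation explains the figure this way: "We have calculated a sample size of 320 patients per group for a population of 100,000 inhabitants", with annual deaths as the starting point. The section then takes about 700 people a year, applies 65% needing specialized palliative care to reach 455, and allows 30% for refusal or ineligibility.

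Three other places bear on the number.

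- Recruitment Procedure defines the intervention group as "those living in the San Pablo-Santa Justa area, Seville (60,000 inhabitants), who accepted the community promoter intervention". No population is given for the control area.
- Trial Design describes a 2-year study. The accrual period is not stated separately. The abstract puts the final analysis after 7 weeks of intervention.
- Sample Size Calculation describes its input as "based on the number of people dying of cancer each year (7000 people per million inhabitants", with about 4500 per million non-oncologic cases named in addition. In the Discussion, Beneficiary Population gives 7000 per million as all deaths, of which "2500 per million die of cancer, and approximately 4500 per million die in the final stage of any nononcologic illnesses".

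**The concern.** A count of how many eligible patients exist cannot by itself yield a power. Power needs a difference, a baseline or SD, a significance level and a sample size. The section that explains 320 contains only the last of these, yet the abstract attaches 80% power to it. Readers will rely on that sentence to interpret a null result: with 80% power for a stated effect, a null result speaks against an effect of that size, and without a basis for the 80% that inference is unavailable.

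The stated effect does not help. It is not said whether 20% is relative or absolute, and no baseline is given. An increase in unmet needs is also the opposite of what the trial hopes to show. Separately, the count is scaled to 100,000 inhabitants while the only named intervention area has 60,000, so the document does not say how many patients that area should supply.

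**Working it through.** **1. Reproducing 320.** Inputs from Sample Size Calculation:

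- 100,000 × 7000/1,000,000 = 700 a year
- 700 × 0.65 = 455
- 455 × (1 − 0.30) = 318.5, rounded to 320

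The figure reproduces as one year's availability. No power input is used.

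**2. What power 320 per group could have.** Alpha is .05 (Statistical Methods). Two-sided testing is assumed, because sidedness is not stated. All baselines are assumed, because none is given. For two proportions:

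power = Φ{ ( |p2 − p1| − 1.96 √[2p̄(1 − p̄)/n] ) / √[ (p1(1 − p1) + p2(1 − p2))/n ] }

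Example, 50% against 60%, n = 320: (0.10 − 1.96 × 0.0393)/0.0391 = 0.585, so power is 72%.

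| Assumed baseline | Relative 20% increase | Relative 20% decrease |
|---|---|---|
| 20% | 23% | 26% |
| 30% | 36% | 40% |
| 40% | 53% | 56% |
| 50% | 72% | 72% |
| 55% | 81% | 80% |
| 60% | 90% | 86% |

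Under the relative reading, 80% power at about 320 requires a baseline near 54% to 55%. For an increase, the required size is 324 at 54% and 309 at 55%. For a decrease, it is 324 at 55%.

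Under the absolute reading (a rise of 20 percentage points), power at 320 exceeds 99.9% for every baseline from 10% to 70%. Only 62 to 97 per group would be needed for 80%.

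**3. Continuous outcome.** The Variables section lists needs, and needs covered by the network, as numbers, so a proportion is only one possible model. The standardized difference detectable with 80% power is (1.96 + 0.842) × √(2/320) = 0.22 SD. No SD is stated, so this cannot be turned into a 20% change.

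**4. Availability in the named area.** The same rates applied to the 60,000 in Recruitment Procedure give:

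- 60,000 × 0.007 = 420; × 0.65 = 273; × 0.70 = 191.1 a year
- Two full years: 2 × 191.1 = 382
- Last 7 weeks of 104 kept for follow-up: 191.1 × 97/52 = 356
- Time to 320: 320/191.1 = 1.67 years, about 20 months

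Loss that still leaves 320: 1 − 320/356 = 10%, or 1 − 320/382 = 16%. The 30% in the plan covers only non-consent and ineligibility. Eligibility Criteria exclude only a life expectancy under 1 week, while the final analysis falls at 7 weeks, so some loss to death must be expected.

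**5. Mortality label.** Beneficiary Population: 2500 + 4500 = 7000 per million, which is 700 per 100,000 and is the figure used. Sample Size Calculation calls the 7000 cancer deaths. The label conflicts with the Discussion; the arithmetic does not.

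**The case against.** The strongest defence is that a journal article condenses a fuller protocol, and the power calculation may sit there. That would answer a silent article. This one has a section saying what 320 was based on, and that basis is a headcount. The coincidence with a relative 20% change from a baseline near 55% does not rescue the claim either, because no such baseline appears.

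Three stronger readings are tempting, and the documents do not support them.

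- *The trial is underpowered.* A reader might infer this from the relative-change column alone. The plan does not say the 20% is relative, and an absolute 20-point rise would be detected almost with certainty. The 80% is unsupported; it is not shown to be missed.
- *The intervention area cannot supply 320.* A reader might compare 191 with 320. But 191 is one year's yield, and nowhere does the plan promise 320 within a year. Over the 2-year study the plan's own rates give 356 to 382. What stands is the thin margin, the assumption of complete capture, and the absence of an allowance for loss after enrolment.
- *The mortality label inflates the sample size.* Adding 7000 and 4500 would suggest so, but the calculation uses 700 per 100,000, which agrees with the Discussion. This is an editorial slip with no effect on 320.

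**Conclusion.** Wrong as written: the abstract presents an availability count as giving 80% power, and the plan's own derivation contains nothing from which power could follow. Depending on what is assumed for the unstated baseline (20% to 60%) and scale, power at 320 per group runs from about 23% to more than 99.9%, so the 80% statement tells the reader nothing usable. These figures assume a two-sided 5% test, independent patients, 320 evaluable per group, and either a proportion or, for the 0.22 SD figure, a continuous outcome.

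The mismatch between 100,000 and 60,000 inhabitants is real and should be reconciled, as a matter of transparency and margin rather than as a proven shortfall. Whether the control area can supply 320 cannot be checked, because its population is not given.

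**What to change.** 1. Delete the 80% power statement from the abstract. Alternatively, name one primary outcome with its scale, the direction of the expected change, and an assumed baseline or SD, and state the difference detectable at 80% power with the expected evaluable number. Correct or explain the direction of the 20% change in unmet needs.
2. Present the availability count separately, for 60,000 inhabitants over the actual accrual period, with an explicit allowance for death and dropout after enrolment. Give the corresponding figure for the control area.
3. Reconcile the mortality label in Sample Size Calculation with Beneficiary Population (2500 cancer + 4500 non-oncologic = 7000 per million).

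Deleting the claim costs one abstract sentence. Replacing it costs more than wording, because the sponsor must first settle on one primary outcome and its assumptions. Items 2 and 3 are a rewritten paragraph. Restating the plan in this way requires no additional patients.

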### Objective

The primary objective of this study is to evaluate the REDCUIDA intervention protocol for the creation and management of networks of care that cover the unmet needs of a person with advanced diseases or at the end of life.

The secondary objectives are to (1) identify the precise nature of a patient’s unmet needs by palliative care teams that can be addressed through mobilization of the community, (2) detect members of the support networks that can meet the patient’s identified needs and describe their fundamental characteristics (caregiver profiles), (3) analyze the influence of a community promoter’s interventions on the emergence and growth of support networks as the disease progresses, (4) assess whether the REDCUIDA intervention improves the patient’s quality of life and decreases the main caregiver’s burden, (5) establish whether this intervention reduces professionals’ workload and health and social resource consumption during end-of-life care, and (6) analyze the influence of the REDCUIDA intervention on the preference of the place of care and death.

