### Hypothesis

We hypothesize that the use of the REDCUIDA protocol in a community intervention program allows for the expansion of care networks that can meet the needs and improve the quality of life of patients, increase family satisfaction, reduce the burden on main caregivers, improve the possibilities of care and death in the preferred place, and reduce the consumption of health care and social care resources during the end of life.

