### Variables

The variables we will use for the descriptive study on the REDCUIDA protocol are the following: for patients’ clinical and sociodemographic data: age, sex, and diagnosis; for families’ sociodemographic data: age, sex, and relationship to the patient; for network of care profiles: relationship to the patient, age, and sex; number of needs according to Barthel Index and the Lawton and Brody scale; number of members of the care network; number of needs covered by the network; quality of life according to the quality of life scale EQ-5D-3L; degree of loneliness according to ESTE II Scale; burden of the principal caregiver according to the Zarit Scale; satisfaction regarding the care network according to the Satisfaction Scale; and place of death.

For community promoter activity data, we will determine the number of interventions performed at home and number of interventions carried out in the community (eg, district, neighborhood, city, community of neighbors).

To assess health care system resources, we will determine the number of hospital admissions in the last month; days of hospital stays in the last month; number of emergency visits in the last month; number of visits of the palliative care team to the home; number of visits of the palliative care team to a hospital; and number of telephone calls made by the palliative care team.

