### Statistical Methods

We will carry out an initial descriptive analysis of variables related to patients’ needs and the profiles of people involved in the social network by degree of kinship.

We will analyze pre- and postintervention data for each group. These will include measures of central tendency (mean), confidence intervals for the 95% average, contingency tables (frequencies), and a linear regression.

To compare the groups, we will compare means. For continuous variables, we will use Student *t* test to compare independent samples with normal distribution and Mann-Whitney *U* test for nonnormal distributions. For discrete variables, we will use Mann-Whitney *U* test. For dichotomous variables (comparison of proportions), we will use Pearson chi-square test. All tests will be carried out with a significance level alpha=.05.

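### The abstract powers the trial for a rise in unmet needs, opposite to the objective, and its primary label conflicts with the Objective section, so no single confirmatory test can be identified

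*Protocol article*

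**What the plan says.** The abstract (Methods) says that 320 patients per group will give the study "80% power to detect a 20% increase in unmet needs". The sentence then adds lower family burden, higher family satisfaction and lower resource use, and ends: "decrease the use of health system resources, the primary end point". Only the change in unmet needs is given a size.

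The Objective section makes the evaluation of REDCUIDA primary, for the "creation and management of networks of care that cover the unmet needs of a person with advanced diseases". Caregiver burden is in secondary objective 4. Secondary objective 5 includes "health and social resource consumption during end-of-life care". The Hypothesis section says that the intervention "allows for the expansion of care networks that can meet the needs and improve the quality of life of patients".

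The Variables section lists the number of needs, the "number of needs covered by the network", and six separate resource counts: admissions, hospital days, emergency visits, team visits at home, team visits in hospital, and telephone calls. It marks none of its variables as primary. Statistical Methods states: "All tests will be carried out with a significance level alpha=.05".

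**The concern.** Two statements that fix what the trial is meant to show are at odds with the rest of the article.

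- **Direction.** An increase in unmet needs is a worsening, yet the objective and hypothesis expect needs to be met. A reader cannot tell whether a decrease in unmet needs or an increase in covered needs was meant, or whether 20% is relative or absolute.
- **Primary outcome.** The abstract's label and the ranking of the objectives cannot both stand.

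At stake is whether the final report can point to one test, chosen in advance, as the test of the intervention. As written, a result on needs could be called primary on the strength of the objective, and a result on resource use on the strength of the abstract.

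**Working it through.** **1. The plan's own figure.** The Sample Size Calculation section gives 700 people a year, 65% needing specialized palliative care, and 30% lost to refusal or ineligibility.

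- 700 × 0.65 = 455
- 455 × (1 − 0.30) = 318.5, about 320

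So 320 reproduces as a count of available patients. That section uses no effect size, alpha or power. The 80% power cannot be re-derived, because no baseline rate, standard deviation or sidedness is given, and it cannot show which effect the authors had in mind.

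**2. Direction, side by side.** Abstract: unmet needs increase. Objective: networks cover unmet needs. Hypothesis: networks meet needs. The abstract is the outlier.

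**3. Does the sign or the scale drive the number?** Assumptions, none stated in the article: the outcome is a yes/no proportion per patient, the test is two-sided at .05, power is 80%, and groups are equal. With p̄ = (p1 + p2)/2,

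n per group = [1.96·√(2p̄(1−p̄)) + 0.8416·√(p1(1−p1) + p2(1−p2))]² / (p1 − p2)²

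Example, 0.50 to 0.40: p̄ = 0.45, and (1.96 × 0.7036 + 0.8416 × 0.7000)² / 0.01 = 387.4, so 388.

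| Assumed baseline | 20% relative decrease: n per group | Power at 320 | 20% relative increase: n per group |
|---|---|---|---|
| 0.40 | 564 (to 0.32) | 56% | 604 (to 0.48) |
| 0.50 | 388 (to 0.40) | 72% | 388 (to 0.60) |
| 0.60 | 270 (to 0.48) | 86% | 244 (to 0.72) |

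A 20-point absolute decrease needs only 62 to 97 per group for baselines 0.30 to 0.80. In this range the sign matters little, while the scale and baseline matter a great deal.

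The two natural corrections also differ. Suppose 0.40 is unmet, so 0.60 is covered. A 20% relative fall in unmet needs goes to 0.32 and needs 564 per group. A 20% relative rise in covered needs goes to 0.60 × 1.2 = 0.72, that is 0.28 unmet, and needs 244.

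**4. The primary label, both readings.**

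- *It covers all four outcomes.* The Objective section ranks burden and resource use as secondary.
- *It covers resource use only.* The Objective section still ranks resource use as secondary, Variables splits it into six counts, and the one stated effect size, on unmet needs, then belongs to a different outcome.

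Neither reading yields one confirmatory test.

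**5. Error rate if all four were primary, each at .05.**

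- Independent tests: 1 − 0.95⁴ = 0.1855
- Upper bound under any dependence: 4 × 0.05 = 0.20
- Lower bound, fully dependent tests: 0.05

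**The case against.** The strongest reply is that this is one wrong word in one abstract sentence. The other three directions in that sentence are beneficial, the Hypothesis section states every direction correctly, and nothing in Statistical Methods makes a test one-sided. The Objective section does give a primary objective, and multiplicity procedures are commonly left to an analysis plan that is not shown here.

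Much of this stands. Some stronger readings are tempting but unsupported:

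- A reader might infer that the trial is designed to detect harm. The objective and hypothesis rule that out; a wording slip is far more likely.
- A reader might take it as settled that four outcomes are primary and that the error rate is 18.5%. The label is singular and may attach to resource use alone. The figure also needs independence, which is unlikely for these outcomes.
- A reader might compute the power lost by splitting alpha four ways. That needs an effect size, which the article does not give for such a calculation; working back from the 80% claim borrows a figure that cannot be reproduced.
- A reader might argue that a raw count of covered needs biases the comparison, because sicker patients acquire more needs. Deterioration can occur in both groups, and the proportion can be formed from the two counts listed, so this is only a reason to prefer the proportion.

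The reply does not remove the conflict between the abstract and the Objective section. A separate analysis plan could settle it only by overriding one of them.

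**Conclusion.** The point holds and should be fixed before outcome data are seen. The article states its one sized effect in the wrong direction and without a scale. It also attaches a primary label that conflicts with its own objectives on either reading. The direction and label conflicts rest on the text alone.

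The sample sizes rest on assumed baselines and a yes/no outcome. They show that the scale must be stated, not that 320 is too few or too many. The range .05 to .20 applies only if all four outcomes are meant as primary.

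**What to change.** 1. Correct the abstract to a 20% decrease in unmet needs, and state whether it is relative or absolute. If a rise in covered needs was intended, say so, since the two are not equivalent on a relative scale.
2. Name one between-group primary outcome consistent with the Objective section, tested two-sided at .05. A natural choice is the proportion of a patient's identified Barthel and Lawton needs not covered by the network; Eligibility Criteria already uses a percentage of uncovered needs. Give the baseline rate or standard deviation behind the power statement; a per-patient proportion needs a standard deviation.
3. Label burden, satisfaction and resource use as secondary or supportive. Family satisfaction needs an explicit place: it is in the Hypothesis but in none of the six secondary objectives.
4. Settle the time point. The Intervention section says V7 re-evaluates needs coverage, but Table 1 ends the Barthel, Lawton and network assessments at V6.
5. Confirm that controls get the same assessment. The schedule is written around promoter visits, and controls live where there is no promoter.

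Items 1 to 3 are mostly rewording. Items 4 and 5 may require extra data collection, which the article does not let one judge. The small downside is that only one outcome then carries the confirmatory claim.
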